#### Additional questionnaires

##### Cognitive reserve index questionnaire (CRIq)

The CRIq [116] has been added posthoc to the testing. It measures cognitive reserve built up over the lifespan. It will be added to the Behavioral Battery at t2 (12 months, see Table 6). Cognitive reserve is the resilience to neuropathological damage in older adults, as a consequence of life-long learning and experiences.

##### Food frequency questionnaire FFQ

The FFQ [91] is used during the pre-screening. It consists of a semi-quantitative questionnaire existing in French and German, on 80 food items divided in 12 food groups. We want to investigate the potential links between quality and quantity of food intake, learning, cognitive functioning, general health and brain function and structure.

#### Progress measures

In order to evaluate the progress in both groups following training, we gather the following measures:

##### Piano group

Evaluation at 3, 6 and 12 months after intervention onset by the teachers, and at 3 and 12 months after intervention onset by professional musicians that do not follow the courses otherwise. The participants are evaluated on 7 different 5-point Likert scales, concerning 1) technique, 2) rhythm, 3) expressivity, 4) text compliance / music reading, 5) ensemble playing, 6) motivation / homework and 7) general progress.A simplified version of Beethoven’s Ode to joy, to be played with both hands on the piano, is recorded (MIDI) after a 2 week preparation at 3 months, at 12 months (end of training) and at 18 months (6 months after course completion).Slow up-and-down playing of a scale of 5 notes at a pace of 76 beats per minutes indicated by a metronome, with 1 note per beat, c-d-e-f-g (so no position change) at the central octave of the piano is recorded (MIDI) at t0, t1, t2 and t3.Fast up-and-down playing of a scale of 5 notes at 76 beats per minute, with 2 notes per beat, c-d-e-f-g (so no position change) at the central octave of the piano is recorded (MIDI) at t0, t1, t2 and t3.The “Genie test”, where participants press the same note (central C) 5 times in crescendo, i.e. increasing the loudness note after note, and 4 times in decrescendo, decreasing the loudness note after note at t0, t1, t2 and t3 (no rhythm to follow)

##### Musical culture / control group

Evaluation at 3, 6 and 12 months after intervention onset by the teachers, and at 3 and 12 months after intervention onset by professional musicians that do not follow the courses otherwise. The participants are evaluated on 6 different 5-point Likert scales, concerning 1) group ambiance, 2) individual participation, 3) interaction (individual), 4) joy (individual), 5) motivation / homework (individual), 6) general progress (individual).A multiple choice questionnaire involving musical knowledge and listening is passed at t0, t1, t2 and t3Slow up-and-down playing of a scale of 5 notes at a pace of 76 beats per minutes indicated by a metronome, with 1 note per beat, c-d-e-f-g (so no position change) at the central octave of the piano is recorded (MIDI) at t0, t1, t2 and t3.

Both groups also complete a training amount questionnaire at 3, 6, 9 and 12 months (see Table 3 “Homework questionnaire”) of intervention, indicating how much time per day and per week each participant spent on homework on average over the last 3 months. These progress and training amount measures will be linked in the final analyses to other brain and behavioral measures.

### Data monitoring and quality assurance

At each site data acquisition and quality is constantly monitored by experimenters for each participant ([name] and [name] in Geneva, [name], [name] and [name] in Hannover). Progress meetings (by Skype) are organized regularly between both sites. A second quality check is performed on the server where all data are backed up (see **Declarations,** Availability of data and materials, p. 16) and analyzed by [name] (see Declarations p. 16). A third checkup is performed by an independant Data Manager (scientific collaborator at PhD level) both at the the HEdS-GE and the HMTMH, after each data point.

We will report reasons for withdrawal of individuals for each randomization group. Exact information on missing data at each time point will be reported in all publications. Missing data will be processed in the analyses with cutting edge means (for instance using the regularized iterative Principal Component Analysis (PCA) algorithm developed by Josse, Husson and Pagès (2009) [117], implemented in the R package missMDA.

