### Design

The study is a two-site Hannover-Geneva longitudinal randomized single blind intervention study in altogether ~ 155 retired healthy elderly (64–78) years, (63 in Geneva, 92 in Hannover, selected according to our inclusion/exclusion criteria out of ~ 500 applications), divided into 2 parallel groups, offering either piano training (intervention group) or musical sensitization training (active control group), both provided by professional musicians.

The active control group serves to control for music listening of similar styles, acquiring general knowledge, social interaction, attentional aspects, weekly instruction away from home, and daily homework.

All participants were informed before enrolling that the study aim is to compare two distinct music interventions and that both may have positive impact on cognitive functioning and brain plasticity (single blind procedure).

In order to prevent strong inhomogeneity between the groups, we use a blocked (“stratified”) randomized design, in order to prevent strong inhomogeneity between the groups at baseline. Stratification involved the factors age, gender, score at the COGTEL^1^ [95, 97] and socioeconomic status. After recruiting all participants, we applied a clustering procedure, separately at each site, to obtain the closest pairs of participants based on the stratification factors. We transformed the latter to z-scores and computed the Euclidian distance between participants, and finally, an algorithm attributed randomly 1 participant of each pair to each group. So, half of the participants ended up in the intervention group, and the other half in the control group at both sites.

Over 12 months participants receive weekly training for 1 hour (we aim at providing 40 courses over the 12 months, adapting to the holidays of the seniors), and also exercise at home for ~ 30 min per day. Participants committed not to miss more than maximum 8 courses on the full curriculum. Both groups study similar different music styles (classical music, world music, jazz, etc.). Subjects will be tested at 4 time points (0, 6, 12 months, and post-training at 18 months) on cognitive, perceptual and motor abilities (Behavioral Test Battery; Table 4), as well as via wide-ranging functional and structural neuroimaging assessments (Table 5).

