#### Power analyses

No standardized computational tools exist for the power analysis of longitudinal neuroimaging studies [129]. A true longitudinal design provides increased statistical power reducing the confounding effects of between-subject variability [130]. Foreseeing an important attrition of 25% in our elderly population, we recruited ~ 30 participants per experimental and per control group in Geneva, and ~ 45 individuals per group in Hannover, so a total of 150 participants. Anticipating around 25% of attrition, final analysis will thus be performed in principle on more than 112 participants, ~ 56 in the experimental and ~ 56 in the control groups.

In order to acquire sufficient statistical power to reliably detect a 2% difference in Gray Matter volume [36] between 2 groups at the whole brain level, a longitudinal study design requires on average 38 subjects, equally divided between the 2 groups [131]. Colcombe and colleagues [81] found reliable frontal GM and WM (White Matter) differences after only 6 months of aerobic training in elderly with much smaller sample sizes (n total = 59, divided evenly over an experimental and a control group) than in this study. To detect reductions in mean tract FA (Fractional Anisotropy, reflects fiber density, measure resulting from Diffusion Tensor Imaging (DTI)) of 2–20%, sample sizes between 7 and 28 subjects are recommended for cross-sectional analyses for an effect size of 5%, depending on the white matter tracts studied [132], but longitudinal studies are more powerful.

Longitudinal intervention studies with 150 participants are rare. All the cited studies involved smaller sample size compared to the current study. Therefore, we consider to have opted for a fair compromise between feasibility of the study and number of participants.

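### The only missing-data method named, PCA completion, would distort the between-arm comparison if used to fill in dropouts' outcomes at the 25% attrition foreseen

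*Protocol article*

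**What the plan says.** **Missing data.** The section Data monitoring and quality assurance promises the reasons for withdrawal by randomised group and the exact extent of missing data at each time point. It continues: "Missing data will be processed in the analyses with cutting edge means (for instance using the regularized iterative Principal Component Analysis (PCA) algorithm", "implemented in the R package missMDA". No other method is named. The text does not say whether the arms are imputed together or separately, whether one or several completed datasets are made, or whether the method is meant for participants who withdraw or for isolated missing tests.

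**Attrition and numbers.** Power analyses gives the recruited number as about 30 per group in Geneva and about "45 individuals per group in Hannover, so a total of 150 participants". It expects heavy loss ("Foreseeing an important attrition of 25% in our elderly population") and concludes: "final analysis will thus be performed in principle on more than 112 participants, ~ 56 in the experimental and ~ 56 in the control groups". The Design section gives a slightly larger number, "63 in Geneva, 92 in Hannover, selected according to our inclusion/exclusion criteria", with equal allocation: "half of the participants ended up in the intervention group, and the other half in the control group at both sites".

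**Arm comparison.** Statistical analyses compares the two groups over the four visits by univariate and multivariate methods with covariates. It names no model that would deal with dropout without imputation.

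**The concern.** Regularised iterative PCA replaces each missing cell by one value taken from a shrunken low-rank fit. A later model that treats this value as measured goes wrong in one of two ways.

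- **Arms imputed together, arm not used.** A dropout's 12-month value is predicted from a structure that does not know the arm. The filled-in quarter carries little of the treatment effect and dilutes the contrast.
- **Each arm imputed separately.** The arm means are preserved, but the filled-in values lie on the fitted surface. The residual variance is too small and the sample is counted as complete, so confidence intervals are too narrow.

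Entering arm as one more column of the PCA gives a mixture of both.

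At stake is the main randomised contrast, piano against musical culture at 12 months. At 25% loss, a routine choice about how to run the imputation would decide between a diluted effect and an inflated error rate. It would also decide whether the analysis counts about 150 or about 112 people.

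**Working it through.** **1. The plan's own figure.** 150 × (1 − 0.25) = 112.5, which agrees with the stated 112, or 56 per arm. From the 155 in the Design section it would be 155 × 0.75 = 116.25. The arithmetic is sound.

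**2. What the choice of number changes.** The article gives no alpha, power or effect size for a cognitive outcome. Assume two-sided 5%, a standardised difference d and an unadjusted comparison of two means:

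- Power = Φ(d·√(n/2) − 1.96). For d = 0.5 and n = 56 this is Φ(2.646 − 1.96) = 0.754. For n = 75 it is Φ(3.062 − 1.96) = 0.865.
- Effect detectable with 80% power = (1.96 + 0.842)·√(2/n), which is 0.53 for n = 56 and 0.46 for n = 75.

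**3. Hand check of the two mechanisms.**

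- Arms together: if a quarter of the 12-month values carry no arm effect, a true 0.50 becomes 0.75 × 0.50 = 0.375.
- Arms separate: the true standard error goes with σ/√112.5. If the filled-in quarter adds no residual variation, the reported one goes with σ·√0.75/√150. The ratio is √(150/112.5)/√0.75 = 1.155/0.866 = 1.33. The effective critical value is 1.96/1.33 = 1.47, a two-sided error of about 14%.

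**4. Simulation.** These settings are assumptions:

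- 75 per arm, visits t0, t1 and t2, one or six tests
- correlation 0.5 or 0.7 between visits, and 0.2 or 0.3 between tests
- 25% missing at t2, half of them already missing at t1, dropout completely at random
- true effect 0 or 0.5 at t2, half of it at t1
- regularised iterative PCA with one or two components
- ANCOVA at t2 adjusted for t0, each completed dataset analysed once as if observed
- 1,000 to 1,500 runs per scenario

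| Handling of dropouts | Mean estimate, true d = 0.5 | Type I error, nominal 5% | True SE / reported SE |
|---|---|---|---|
| Left out | 0.49–0.51 | 0.04–0.06 | not tabulated |
| PCA, arms together, arm not used | 0.38–0.39 | 0.04–0.05 | 0.96–1.04 |
| PCA, arm as a column | 0.41–0.44 | 0.05–0.10 | 1.00–1.20 |
| PCA within each arm | 0.49–0.51 | 0.12–0.14 | 1.30–1.38 |

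Shrinkage is (0.50 − 0.39)/0.50 = 22% to (0.50 − 0.38)/0.50 = 24% with arm ignored, and 11 to 18% with arm as a column.

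A variant with eight tests (correlations 0.7 and 0.3) agrees. With arms together the estimate is 0.39, and the 95% interval covers the truth 84% of the time. Within arm, the reported SE is 0.109 against a true 0.139, with type I error 13% and coverage 87%.

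**The case against.** The best defence is that the text fixes very little. PCA is introduced as an example, and the article never says that a single completed dataset will be used. Whether arm enters the imputation, and how its uncertainty is carried forward, are details that a condensed article may leave to the full plan. A long test battery, five MRI measurements and optional blood samples at four visits will produce scattered gaps, and the imputation may be meant only for those, among people who stay. The simulated harm would then not arise. PCA completion is also a natural step before the planned ICA and PLS analyses.

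Much of this stands, and three stronger readings should be resisted:

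- **That the plan commits to single PCA imputation of dropouts.** It does not. The harm is conditional on that use.
- **That the power section contradicts the imputation by defining a completer set.** Its 112 is worded as a planning floor. It does not speak of completers and defines no analysis set.
- **That leaving dropouts out would itself be biased.** Under the random dropout simulated here it was not. Bias needs dropout related to arm or performance, which was not simulated.

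What does not stand is the claim that this is only missing detail. The article names a method, names no alternative, places it straight after withdrawals and does not limit its use. Reporting withdrawals and missing data openly is good practice, but it does not repair an estimate.

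**Conclusion.** The point holds in conditional form and is worth acting on. The one missing-data method that the article names is unsuitable as a one-off completion of dropouts' outcomes before the between-arm comparison, and nothing in the article rules that use out. At the foreseen 25% attrition it would shrink the arm effect by about 11 to 24% when the arms are imputed together, or raise a nominal 5% error to about 12 to 14% when they are imputed separately. In every scenario run, at least one of the two faults appeared.

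The sizes depend on the assumed correlations, on completely random dropout, and on dropouts' 12-month values being imputed. With imputation confined to scattered gaps among retained participants, these figures do not apply. The 112 contains no error. It only leaves open whether dropouts are imputed or left out.

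**What to change.** 1. **Between-arm comparisons.** Use a likelihood-based repeated-measures model on all observed visits of all randomised participants, with arm by visit, the baseline outcome and the randomisation factors (age, gender, COGTEL score, socioeconomic status, and site, because pairs were formed within site). Outcomes are not imputed.
2. **Inference that needs a complete matrix.** Use multiple imputation with arm and visit in the imputation model, and pool the results by Rubin's rules.
3. **Single PCA completion.** Keep it for exploratory multivariate work, and say so where the method is named.
4. **Power text.** Describe 112 as the number expected still to provide outcome data after attrition.

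The model in step 1 assumes that dropout depends only on observed data. The withdrawal reasons by arm, already promised, will help to judge that.

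The cost is a change of analysis wording and standard software, with no new data, visits or participants. Confidence intervals will be wider than under single imputation, because they no longer count filled-in values as measured.

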### Statistical analyses

First, we will study cross-sectionally all relationships between behavior and brain data collected at baseline (data from t0) for all participants (1) based on a priori hypotheses using general linear models, correlations and regression analyses; (2) Using data-driven multivariate approaches that allow to reveal more intricate relationships between the data.

Brain data will mostly be analyzed using in-house script routines calling the last versions of the standard neuroimaging software pipelines (SPM12, FSL6, FreeSurfer, MRtrix etc.), all running on the same operating system on our server (Linux xfce4.12) to avoid any potential operating system bias [118].

Second, we will examine and compare the development in both experimental groups over time (t0 vs. t1 vs. t2 vs. t3) for the comprehensive set of behavioral and brain data using univariate and multivariate methods. Individuals’ intensity of training, progress, demographic characteristics and post-hoc appreciation of the courses will be taken into account (implemented as co-variates).

Analyzing separately behavioral data and several kinds of brain imagery data cross-sectionally or over time provides valuable information on these specific data. However, blending diverse behavioral and different kinds of brain data within data-driven multivariate analyses may unravel hidden “covert” relationships [119, 120]. For these advanced analyses we will be assisted by Prof. [name], computer scientist; expert in advanced (f)MRI data analyses).

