Trust agreement	Before the courses start	The participant declares aiming to perform homework at least 30 min per day, 5 times per week, not to miss more than maximum 8 courses (on 40 in total), and announce absences and holidays well in advance with reasons and not to engage in any supplementary musical education	Read & Sign	Participant & member research team
MRI safety questionnaire	Before MRI measurements	Questions assuring MRI compatibility	Read & Sign	Participant & MRI operator
Debriefing on the fMRI task	After MRI measurements	Answer questions on sound perception, comprehension of the task, rating of difficulty of different experimental conditions, used strategies to perform the task, remarks	Read, answer questions	Participant & member research team
Homework questionnaire	3, 6, 9 & 12 months after the beginning of the music interventions	Time per day and per week spent on homework on average	Read and -sign	Participant

Consent to voluntary participate to the study involved: the right to withdraw at any time, accepting the use of the collected data for scientific and educational purposes –with the assurance that the data will remain anonymous-, to accept blood sampling or not -on a voluntary basis- and finally, whether to inform the participant or his or her treating physician in the event of unexpected potential detection of abnormalities.

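### The piano-versus-control comparison is adjusted for training intensity, progress and course appreciation, which arise after randomisation, so the adjusted coefficient is not the effect of assignment to piano

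*Protocol article*

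**What the plan says.** Under Statistical analyses, the second step of the plan is the randomised comparison: "we will examine and compare the development in both experimental groups over time (t0 vs. t1 vs. t2 vs. t3"), for the full set of behavioural and brain data. The next sentence names what enters it: individuals' "intensity of training, progress, demographic characteristics and post-hoc appreciation of the courses will be taken into account (implemented as co-variates").

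The article shows when two of these covariates are collected, and the name of the third places it after the course:

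- **Training intensity.** The homework questionnaire (Table 3) is completed "3, 6, 9 & 12 months after the beginning of the music interventions", by both arms, "indicating how much time per day and per week each participant spent on homework on average over the last 3 months".
- **Progress.** Piano group: "Evaluation at 3, 6 and 12 months after intervention onset by the teachers", with outside musicians also rating at 3 and 12 months. The control group follows the same timetable. The instruments differ. For piano, "The participants are evaluated on 7 different 5-point Likert scales, concerning 1) technique, 2) rhythm", and so on. For controls, "The participants are evaluated on 6 different 5-point Likert scales, concerning 1) group ambiance, 2) individual participation", and so on.
- **Appreciation of the courses.** It is described as post hoc.

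A further adjustment is stated elsewhere: the (f)MRI measurements section and the Discussion both plan a scanner covariate in all analyses. Each site has its own scanner, so this also serves as a site term.

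**The concern.** Randomisation makes the arms comparable on everything fixed before assignment. That protection does not cover variables that the assigned course can itself change. The trial's hypothesis is that practising the piano produces the benefit. Holding practice time or progress constant may therefore hold constant part of the mechanism under test. Motivation is a plausible common cause of homework time and test performance. If the arm also shifts homework time, conditioning on it brings motivation into the arm comparison as a confounder, which randomisation had excluded.

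Progress raises an additional problem. A rating of technique or expressivity at the piano does not measure the same thing as a rating of group ambiance or joy in a listening class.

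At stake is the piano-versus-control contrast on which the primary outcomes rest. No section states an arm comparison without these covariates, and none confines them to a secondary analysis.

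**Working it through.** **1. The plan's own figure.** Power analyses: 2 × 30 + 2 × 45 = 150 recruited. With 25% attrition, 150 × 0.75 = 112.5. This agrees with the article's figure of more than 112, or about 56 per arm, and 56 per arm is used below. The article gives no alpha, power or SD for a cognitive outcome, so it has no power figure to reproduce for one.

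**2. Classification of the covariates.**

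| Covariate | When it arises | Can the assigned course change it? |
|---|---|---|
| Demographics | Pre-screening | No |
| Training intensity | Months 3, 6, 9, 12 | Yes |
| Progress | Months 3, 6, 12 | Yes |
| Appreciation | Post hoc | Yes |

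**3. Overlap of the progress scales.** Piano has 7: technique, rhythm, expressivity, music reading, ensemble playing, motivation/homework, general progress. Control has 6: group ambiance, participation, interaction, joy, motivation/homework, general progress. Two are shared by name, leaving five piano items and four control items with no counterpart.

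**4. Shared-cause illustration.** These inputs are assumptions, not taken from the documents. Covariate H = a·arm + 0.6U + 0.8e. Outcome Y = d·arm + 0.4U + noise of variance 0.84. U is unmeasured motivation, and H and Y have unit variance within arm. The within-arm correlation is 0.6 × 0.4 = 0.24, so regressing Y on arm and H gives an arm coefficient with expectation d − 0.24a. Its standard error is approximately √[(1 − 0.24²)(2/56 + a²/110)]. For a = 0.5 this is √[0.9424 × (0.0357 + 0.0023)] = 0.189.

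| Shift a (SD) | Bias = −0.24a | False positives at nominal 5% | Estimate when d = 0.5 | Power at d = 0.5 |
|---|---|---|---|---|
| 0 | 0 | about 5% | 0.50 | about 76% |
| 0.2 | −0.05 | about 6% | 0.45 | about 67–68% |
| 0.5 | −0.12 | about 9% | 0.38 | about 51% |
| 1.0 | −0.24 | about 21% | 0.26 | about 24% |
| −0.5 | +0.12 | about 9% | 0.62 | inflated |

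Simulation with 20,000 replicates per row agrees with these approximations. In this model the sign of the estimate reverses whenever 0 < d < 0.24a.

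**5. Mediation illustration.** Assume a total effect of 0.5 SD and a covariate shifted by 0.5 SD. If half the effect passes through the covariate, its slope is (0.5 × 0.5)/0.5 = 0.5, and the adjusted coefficient is 0.5 − 0.5 × 0.5 = 0.25. Simulated rejection falls from 0.74 to 0.30. If all of it passes through, the slope is 1, the coefficient is 0.5 − 1 × 0.5 = 0, and rejection is 0.05. If none passes through and there is no shared cause, the coefficient stays at 0.50.

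**The case against.** The best case for the plan has four parts.

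- **Bias is conditional.** It needs the arm to shift the covariate. Both arms have the same targets: one lesson a week, at most 8 of 40 missed, and homework of at least 30 minutes five times a week. If homework time ends up similar across arms, adjusting for it does little harm; the rows for 0 and 0.2 SD show this. This stands. A reader might infer that the comparison is certainly biased, but no section says that homework or appreciation will differ between arms.
- **Progress may not be a pooled score.** Both instruments use 5-point scales, the rating months are the same, and two items share a name. Both arms also record the slow five-note scale. The article does not say which progress variable is the covariate or that the items are combined. A reader might infer a single score largely confounded with arm, and the text does not go that far. Most items nonetheless have no counterpart, and the two with shared names refer to different courses.
- **No main model is named.** The section speaks of univariate and multivariate methods in general. The progress section says that progress and training amount will be linked to outcomes, which fits a dose-response use. It would therefore be too strong to say that the benefit of randomisation is lost in the main analysis.
- **It is a condensed article.** An analysis plan may add detail. However, this concerns a stated choice, placed directly after the arm comparison, which such a plan would have to reverse.

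Nor are these the only covariates stated, since the scanner term is also planned.

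**Conclusion.** The point holds as a defect in the stated rule. Three of the four kinds of covariate named for the randomised comparison arise after randomisation and can be affected by the course. Nothing in the article limits them to another analysis. With them in the model, the arm coefficient is not the effect of being assigned to piano, and this conclusion needs no numerical assumption.

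The amount of distortion does depend on assumptions. Bias arises if the arm shifts a covariate and that covariate either mediates the effect or shares unmeasured causes with the outcome. Under the assumed correlation of 0.24, it runs from nil at no shift to −0.24 SD at a shift of 1 SD, and it changes sign if the shift does. Full mediation would remove the effect altogether. The documents support neither a particular size nor a particular direction.

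**What to change.** Remove training intensity, progress and post-hoc appreciation from the covariates of every piano-versus-control comparison. State that these comparisons are made by assigned arm and adjusted for baseline variables only: the t0 value of the outcome, the scanner/site term already planned, and the stratification factors (age, gender, COGTEL score, socioeconomic status).

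Use the three post-randomisation variables only in separately labelled exploratory analyses, either within-arm dose-response or mediation, with a note that these are not protected by randomisation. Where progress is used, say which items enter. This keeps the interest in how much practice matters.

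The cost is a revision of the Statistical analyses wording. No new data are needed.
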